|  | 
influence; Way: coercive possibility or undue Affect to minimize
 
for of the study subject research Participation Whether the decision is voluntary will, research take part reject or research term middle whenever freely take part to stop Number and by to stop Number and by teeth Because on the next treatment any no teeth Because next in treatment any disadvantage Not at all disadvantage at all take it won't and that consent to participate in the study take it won't will, whenever Participation in research consent to may be withdrawn at any time. inform
 
withdraw Number that there is inform
 
research Explanation process and agreement acquisition In progress researcher using language : Korean
 

• research subject or his/her representative can understand language: Korean

• study subjects or to the agent provided information and agreement Format: consent and manual offer

 | 
To minimize the possibility of coercion or undue influence of the study subject research Participation Whether the decision is voluntary will, research take part reject or research term middle whenever freely take part to stop Number and by to stop Number and by teeth Because on the next treatment any no teeth Because next in treatment any disadvantage Not at all disadvantage at all take it won't and that consent to participate in the study take it won't will, whenever Participation in research consent to may be withdrawn at any time. inform
 

• research Explanation process and agreement acquisition In progress researcher using language: Korean

• study subjects or agent understand Number there is language: Korean

 
study subjects or to the agent provided information and agreement Format: consent and manual offer
 |  |
|--|------------------------------------------------------------------------------------------------------------------------------------------------------------------------------------------------------------------------------------------------------------------------------------------------------------------------------------------------------------------------------------------------------------------------------------------------------------------------------------------------------------------------------------------------------------------------------------------------------------------------------------------------------------------------------------------------------------------------------------------------------------------------------------------------------------------------------------------------------------------------------------------------------------------------------------------------------------------------------------------------|---------------------------------------------------------------------------------------------------------------------------------------------------------------------------------------------------------------------------------------------------------------------------------------------------------------------------------------------------------------------------------------------------------------------------------------------------------------------------------------------------------------------------------------------------------------------------------------------------------------------------------------------------------------------------------------------------------------------------------------------------------------------------------------------------------------------------------------------------------------------------------------------------------------------------|--|

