### **4) Target number of subjects and calculation basis**

- GMFCS IV and V patients were combined before wearing auxiliary equipment, MI progression / year was measured to be  $7.83 \pm 8.73\%$  (set as a control group) (APMR 2019, IS [name], JS [name], etc.) when data.)
- In this study, the MI of the experimental group was set to  $1.566 \pm 8.73\%$ , assuming that the MI decreased by 80% when wearable auxiliary medical devices were worn.
- When the number of study subjects calculation program (PASS 15.0) was used with Level of significance = 5%, Power = 80%, and Type of test = two-sided, the total sample size was calculated as 32 patients per group and 64 patients in total, and 5% of Considering the dropout rate, a total of 68 experimental and control groups will be recruited.

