## 12. Specific research methods

Patients diagnosed with severe cerebral palsy were included in the study.

Assignment to experimental group and control group if consent to the study

Subject's body measurements were performed to measure the size of the hip joint wearable medical device.

Radiologic and clinical evaluation were performed to evaluate hip dislocation.

The experimental group manufactured and applied hip-joint wearable medical devices, continue existing rehabilitation treatment.

The control group continued the existing rehabilitation treatment.

6 months and 1-year, clinical evaluation and radiological evaluation were performed to determine the effectiveness.

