**(1) Data analysis and statistical analysis method**

1. Primary efficacy endpoint: hip dislocation through radiographic evaluation (%)
2. Secondary efficacy endpoints: degree of scoliosis through plain radiograph; pain index, Functional changes such as satisfaction with wearable medical devices for hip joint protection, hip and knee joint range of motion, discomfort when caring for a patient, and changes in the patient's overall quality of life were investigated.

The clinical evaluation is statistically compared between the initial and simple X-ray results after 1 year (compare with paired t-test or Wilcoxon signed rank test according to normality test). In addition, the difference in change values for the initial, 6 months, and 1 year after simple X-ray imaging and clinical evaluation is statistically compared. Repeatedly measured values are verified by a linear mixed model or a generalized estimating equation (GEE) between the experimental group and the control group. If the P-values are  $< 0.05$ , it is judged to be a significant level.

Dropout, all data including in statistical processing (ITT) will be analyzed through safety and efficacy evaluation, unless there is a valid reason or justification. When missing values occur in the FAS group, they are excluded and analyzed because it is difficult to satisfy the assumption of Missing Completely at Random (MCAR).

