|     | 
Method
 
data analyze and statistics analyze Method/19p
 
retation Method (statistical analysis method , etc. )
 | 
1. Primary efficacy endpoint: hip dislocation through radiographic evaluation (%)
 
scoliosis, pain index, and hip joint protection through plain radiograph wearable
 
Functional changes such as satisfaction with medical devices, hip and knee joint range of motion, discomfort when caring for a patient, and changes in the patient's overall quality of life are identified.
 
The initial and 1-year plain X-ray results were compared statistically (by Wilcoxon matched pairs signed rank test). The difference in change values is verified by Mann Whitney U test between the experimental group and the control group. If -values is < 0.05, it is judged to be a significant level. Dropouts are analyzed for all data including in statistical processing (ITT) through safety and efficacy evaluation, unless there is a justifiable reason or evidence, and PP analyzes by excluding dropouts and patients with data omissions.
 | 
1. primary effectiveness evaluation variable: radiation evaluation through hip jointdislocation (%)
 
2. secondary effectiveness evaluation variable: simple radiation check through scoliosisDegree, ache Indices, hip joint protect wearable of medical devices satisfaction,
 
hipclass kneeof joint range of motion, the patient take care at the time discomfort, patient'soverall of life vaginal change Such as functional change find out.
 
early and one year later simple X-ray filming result, clinical evaluation statistically Compare (normality on black according to Paired t-test or Wilcoxon signed rank test as compare). Also, early and 6 months After, 1 year after simplicity X-ray results and clinical for evaluation change of value make the difference statistically Compare. repeat measured on the value about between the experimental group and the control group linear mixed model or Generalized estimating with equation (GEE) verify P-values go < 0.05 Work case significant to the level judge midway dropped out sleeping proper Reason or grounded Do not have one safety,effectiveness evaluation through statistics to processing
 | 3.                                                                                                 |

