#### 2.3.2 Sample Size Determination

A. The calculation of the sample size is based on the previous epidemiologic study ([name] IS, Park D, Ko JY, [name] JS. Are Seating Systems With a Medial Knee Support Really Helpful for Hip Displacement in Children With Spastic Cerebral Palsy GMFCS IV and V? *Arch Phys Med Rehabil* 2019; **100**(2): 247-53.).

B. In this study, the annual progression of MI in patients with severe cerebral palsy (GMFCS IV and V) was measured to be  $7.83 \pm 8.73$  %. Assuming the MI decreased by 80 % applying Hip protection brace, the MI of the study group was set to  $1.566 \pm$

8.73 %.

C. We used PASS 15.0 for two-sample T-Test assuming equal variance.

D. With an  $\alpha$  of less than 0.05 in the two-tailed tests and a power of 80%, the target sample size of each group is 32 patients.

E. Considering a dropout rate of 5 %, the final sample size was determined to be 68 patients per group.

F. This clinical trial compares the post-treatment changes between the study and the control groups. This study was the superiority trial to show the significant improvement of the MI in the study group than the control group.

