## 1.7 Data Analysis and Statistical Analysis Methods

- The clinical evaluation is statistically compared between the initial and simple X-ray results after 1 year (compare with paired t-test or Wilcoxon signed rank test according to normality test).
- In addition, the difference in the change values for the initial, 6 months, and 1 year after simple X-ray imaging and clinical evaluation is statistically compared.
- Repeatedly measured values are verified with a linear mixed model or Generalized estimating equation (GEE) between the experimental group and the control group.
- If the P-values are  $< 0.05$ , it is judged to be a significant level.
- All data, including those included in statistical processing (ITT) through safety and efficacy evaluation, will be analyzed for those who are dropped out unless there is a valid reason or justification.
- In the case of missing values in the FAS group, it is difficult to satisfy the assumption of Missing Completely at Random (MCAR), so it is excluded and analyzed.

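### Paired initial-to-1-year tests share one p < 0.05 rule with the between-arm model, and the plan does not make them descriptive

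*Combined protocol and SAP*

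**What the plan says.** Three current places carry the same analysis list: protocol version 13.0, section 17(1); the statistical row of its Study Overview; and SAP version 13.0, section 1.7. SAP 1.7 opens with "The clinical evaluation is statistically compared between the initial and simple X-ray results after 1 year (compare with paired t-test or Wilcoxon" signed rank test, chosen by a normality test. Protocol 17(1) has the same opening: "The clinical evaluation is statistically compared between the initial and simple X-ray results after 1 year". The translation is rough, but the change table shows that both X-ray results and clinical evaluation are meant: "early and one year later simple X-ray filming result, clinical evaluation statistically Compare (normality on black according to Paired t-test or Wilcoxon".

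All three places then add a comparison of change values at the initial visit, 6 months and 1 year, and a between-arm linear mixed model or GEE for the repeated measures. One p < 0.05 rule follows. In SAP 1.7 that rule is a separate bullet after the three analysis bullets.

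Other parts of the SAP point to the control comparison:
- 2.3.1 and 4.8 state the hypothesis as equal change in the two arms.
- 2.3.2 F says the trial compares post-treatment changes between groups.
- 4.13, on assessment of effectiveness, names only the between-arm model.
- 2.3.2 C sizes the trial on a between-arm test: "We used PASS 15.0 for two-sample T-Test assuming equal variance".

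**The concern.** A paired test asks whether children changed over a year. The trial's hypothesis asks whether the two arms changed by different amounts. The paired test cannot answer that, because it makes no use of the control arm.

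Change without any brace effect is to be expected here. The children are aged 1 to 10 and growing. Rehabilitation goes on in both arms; for the controls, protocol section 12 says "The control group continued the existing rehabilitation treatment". The sample size itself assumes that MI worsens by 7.83 points a year without the device.

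Nothing limits the p < 0.05 rule to the between-arm model. A report could therefore call a within-arm change significant, or set a significant worsening in the control arm beside a non-significant one in the brace arm, and still comply with SAP 1.7. A reader would take either as evidence about the brace. The secondary outcomes are the most exposed, since no between-arm power is planned for them.

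**Working it through.** **Inputs.** From protocol section 10, target number of subjects: control MI progression 7.83 per year, brace arm 1.566, SD 8.73 in both; "Level of significance = 5%, Power = 80%, and Type of test = two-sided"; "32 patients per group and 64 patients in total"; 5% dropout.

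**1. The plan's own figure.** Difference = 7.83 − 1.566 = 6.264. With 32 per arm, the standard error is 8.73 × √(2/32) = 2.1825 and the noncentrality is 6.264 / 2.1825 = 2.87. The exact noncentral t gives power 80.7% at 32 per arm and 79.4% at 31, so 32 is reproduced. Dropout: 32/0.95 = 33.7, so 34 per arm and 68 in total, which agrees with the protocol ("a total of 68 experimental and control groups will be recruited"). SAP 2.3.2 E writes 68 per group; the calculation supports 68 in total. The trial is thus sized on the between-arm comparison.

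**2. Which outcomes can be paired.** The study schedule records range of motion, pain and CPCHILD before the device is worn. Sections 14(4), 14(2) and 14(3) state initial measurements for MI, Cobb angle and femur anteversion. Satisfaction is collected only at 180 and 360 days, so an initial-to-1-year test of it is impossible.

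**3. Paired test under a common drift.** Let both arms change by d SDs of the change score, with no brace effect. For one arm of n = 32, the statistic is noncentral t on 31 degrees of freedom with noncentrality d√32, and the test is two-sided at 5%. The documents give no drift for the clinical outcomes, so d is hypothetical.

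| Drift d (SD) | d√32 | Paired test significant in one arm (n = 32) | Paired test significant if arms are pooled (n = 64) | Between-arm test |
|---|---|---|---|---|
| 0 | 0 | 5% | 5% | 5% |
| 0.2 | 1.13 | 20% | 35% | 5% |
| 0.3 | 1.70 | 38% | 66% | 5% |
| 0.5 | 2.83 | 78% | 98% | 5% |
| 0.8 | 4.53 | 99% | 100% | 5% |

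The common drift cancels from the between-arm contrast, so that test stays at its nominal level. A simulation of 100,000 trials at d = 0.5 gave 4.9% for it and 78.6% for the paired test.

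**4. MI, where the plan gives figures.** At the control rate, d = 7.83/8.73 = 0.897, the noncentrality is 5.07 and the paired test is significant with probability 99.8%. At the assumed brace rate, d = 1.566/8.73 = 0.179, the noncentrality is 1.01 and the probability is 16.6%.

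**5. The pattern of control significant and brace not, with no brace effect.** If each arm's paired test is significant with probability p, and the arms are independent, the pattern has probability p(1 − p). That is 23% at d = 0.3 and 17% at d = 0.5, and it cannot exceed 25%. For MI with both arms at 7.83 it is 0.2%.

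**The case against.** The strongest reply is that the plan already puts effectiveness where it belongs. SAP 2.3.1, 2.3.2 F, 4.8 and 4.13 and the sample size all refer to the contrast between arms. The paragraphs that contain the paired test also contain the between-arm model, and in protocol 17(1) the threshold sentence comes directly after it. A reader might infer from the order of the list that the paired test is the efficacy analysis. The documents do not support that: no text ranks it as primary, and none says that a significant paired result shows a brace effect. A reader might also infer that every outcome is affected; satisfaction is not.

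The reply on size is fair too. When children truly change, rejecting no change is correct for the paired test's own null. The percentages above become false claims only if that result is read as a brace effect. The drifts are chosen values, and the text does not say that the tests are run per arm. MI is expected to worsen, so a significant paired result in the brace arm would count against the device. The misleading contrast of one significant arm and one not is rare for MI at the planned rate, at 0.2%.

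All of this narrows the point, but it does not remove it. SAP 4.13 says what is used for effectiveness. It does not withdraw the first bullet of SAP 1.7, and it does not confine the separate p < 0.05 bullet to the model.

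**Conclusion.** The point holds as a gap in permitted inference, of minor to moderate weight. The plan prescribes paired significance tests that cannot address its own hypothesis, places them under the same threshold as the between-arm model, and does not call them descriptive or say whether they are per arm or pooled. For MI, Cobb angle, femur anteversion, range of motion, pain and CPCHILD, a change shared by both arms can be declared significant when the brace does nothing.

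Run per arm with 32 children, the probability is 20% to 99% for an assumed drift of 0.2 to 0.8 SD, and 99.8% for MI at 7.83 per year. These figures rest on normally distributed changes, the same drift in both arms and, except for MI, hypothetical drift values. They do not mean that the error rate of the effectiveness test is inflated: that test is between arms and stays at 5% under a common drift.

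**What to change.** In SAP 1.7 (first bullet), protocol 17(1) and the Study Overview:
- Replace the paired t-test and Wilcoxon signed rank test with the mean change from initial visit to 1 year in each arm, with a 95% CI, reported as description and without a significance declaration.
- Restrict the p < 0.05 rule to the between-arm contrast in change, in agreement with SAP 2.3.1, 4.8 and 4.13.

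A single sentence stating that the paired tests are descriptive, and that efficacy conclusions rest only on the between-arm model, would remove most of the ambiguity. Leaving out the p-values is cleaner.

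The cost is wording. Visits, data and sample size are untouched, and the sponsor gives up only the within-arm p-values.

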# Statistical Analysis Plan, Version 2.0

## 1.0 Introduction

This Statistical Analysis Plan (SAP) describes the statistical analyses planned to address the objectives of the clinical trial. It details the analyses that will be performed to accomplish these objectives. This SAP defines variables and identifies methods and algorithms used to populate the tables, figures, and listings that are included in reports for this study.

## 2.0 Study Design

### 2.1 Objectives

#### 2.1.1 Primary Objectives

The primary purpose of this study is to investigate the purpose of our study was to investigate the efficacy of newly designed hip protection brace applying biomechanical factor for preventing progressive hip displacement in patients with severe CP in a single-blinded randomized clinical trial (RCT).

#### 2.1.2 Secondary Objectives

The second purpose is to investigate the safety of hip protection brace.

### 2.2 Study Hypotheses

Our hypothesis is that hip protection brace can stabilize the hip joints, reduce the activation of hip adductors, and assist the protective function of ligaments and muscles around hip joints, thereby decreasing the progression of hip dislocation.

### 2.3 Sample Size Determination

#### 2.3.1 Statistical Hypotheses

the null hypothesis is as following.

$H_0$  = There is no meaningful relationship in migration index (MI) between the two groups. ( $H_0: U_t = U_c$ ).

$H_1$  = There is significant differences in MI between the two groups. ( $H_1: U_t \neq U_c$ ).

$U_t$  = MI (Post, test group) - MI (Pre, test group),  $U_c$  = MI (Post, control group) - MI (Pre, control group).

#### 2.3.2 Sample Size Determination

- A. The calculation of the sample size is based on the previous epidemiologic study ([name] IS, Park D, Ko JY, [name] JS. Are Seating Systems With a Medial Knee Support Really Helpful for Hip Displacement in Children With Spastic Cerebral Palsy GMFCS IV and V? *Arch Phys Med Rehabil* 2019; **100**(2): 247-53.).
- B. In the previous study of this researcher, the MI of GMFCS IV and V patients before wearing auxiliary equipment was measured to be  $26.89 \pm 17.10\%$
- C. In this study, the MI of the experimental group was set to  $16.134 \pm 17.1$  and  $13.445 \pm 17.1$ , respectively, assuming that the MI decreased by 40% for GMFCS IV and 50% for GMFCS V when wearable auxiliary

medical devices were worn.

D. We used (G-power 3.1.9.2) for two-sample T-Test assuming equal variance.

E. With an  $\alpha$  of less than 0.05 in the two-tailed tests and a power of 80%, the target sample size of each group is 11 patients. Considering a dropout rate of 5%, the total sample size was calculated as 11 each in the experimental group and control group for GMFCS IV, and 8 each in the experimental group and control group for GMFCS V. Considering the dropout rate of 10%, a total of 42 experimental and control groups will be recruited.

F. This clinical trial compares the post-treatment changes between the study and the control groups. This study was the superiority trial to show the significant improvement of the MI in the study group than the control group.

## **2.4 Blinding**

This clinical trial is conducted with single blinded (covering the eyes of the evaluators) to minimize bias. For blinding of the evaluators, all evaluators are blinded to the group allocation and blinded the clinical information.

Only the random assignment officer and the therapist (the researcher) who conducted the intervention are aware of the information about the group allocation. But the independent evaluators are kept blinded. After all test results are saved as images or entered into the database and database locking, the person in charge can know the randomly assigned results.

## **2.5 Assessment**

The assessment will be performed by two independent physiatrists who have certificate.

## **2.6 Randomization and Enrollment**

In order to prevent an imbalance in the number of study subjects between the experimental group and the control group, a block randomization method is adopted. Randomization was performed using Microsoft Excel program. 24 GMFCS IV and 18 GMFCS V subjects were randomly assigned to two groups with a block size of 4 and an allocation ratio of 1:1. In the header of cells A1, B1, C1, and D1 of the Excel spreadsheet, enter Sequence, Random number, Block, and Group, respectively. ① Enter the numbers from 1 to 24 and 1 to 18 in cell A, which is the Sequence column, in order, and ② enter the function = Rand() in B of the Random number column to assign a random function. ③ In block column C, repeat the numbers 1 to 6 and 1 to 4 in order. At this time, the numbers 1 to 4 or 6 are repeated 4 times, which means that 24 and 18 study subjects were assigned a block size of 4. ④ In the Group column, input the experimental group and the control group, respectively, followed by 12 and 9 people. Then, drag from B1 to D1 to select it, and select Home -> Sort & Filter -> Filter. When there is a scroll bar in each cell, click

the scroll bar in C1 to select ascending sort, and then click the scroll bar in C1 to sort in ascending order to complete the randomization table (Kang, 2017). A random number table is created, and a new random function is generated at the start of the study. At this time, the random number on the sheet may change and the assignment may be changed, so copy or capture the value and keep it.

